## Abstract

**Introduction:**

Despite guideline recommendations, inpatients with mental health disorders often do not receive appropriate treatment after discharge. This leads to high readmission rates, problems with medication adherence, increased risk of chronicity and suicide, and exclusion from the labour market accompanied by high individual and social costs. The causes are both system-related, such as limited treatment availability, and patient-related, such as ambivalent motivation to continue treatment and lack of information about available treatment options. The aim of this trial is to assess the feasibility of a Care Transition Intervention (CTI) which supports patients in the psychosocial follow-up treatment process after discharge from a psychotherapy ward.

**Methods and analysis:**

Fifty patients with depression and/or anxiety who are treated as inpatients at a psychotherapy ward will be included and randomised into two groups with a 1:1 ratio. In the intervention group, patients will receive five CTI sessions with a Care Transition Navigator before and after discharge. The sessions will focus on individual patient support including a) identification and tackling of barriers to initiate follow-up treatment, b) reflection on the inpatient stay and individual progress, with focus on the helpful aspects and c) motivation of patients to organise and take up outpatient treatment. Patients in the control group will receive treatment-as-usual during discharge. We will evaluate the following outcomes: effectiveness of recruitment strategies, patient acceptance of randomisation, practicability of implemented workflows, feasibility of data collection, and clinical outcomes.

## Introduction

For patients with mental illness, the transition from inpatient to outpatient care is crucial. However, it is at this point that the continuity of care is often interrupted [1–3]. Patients have issues finding their way in the commonly indicated outpatient follow-up treatment. This leads to several negative effects such as; high readmission rates, problems with medication adherence, increased risk of chronicity and suicide, and exclusion from the labour market accompanied by high individual and social costs [1, 3–8]. Reasons for not starting outpatient follow-up treatment are on a structural (low treatment capacities of mental health specialists) as well as individual level (ambivalent motivation towards further treatment, lack of access to information about available treatment options and resulting difficulties in navigating through the health care system [9–11]).

While the barriers at the individual level appear obstructive, they are modifiable in the short term [12]. Patients often need support to prepare for the time after discharge and to orient themselves in the complex system of outpatient psychosocial care. This is where Care Transition Interventions (CTIs) come in, by providing close support for individual patients at an early stage, i.e. before and shortly after discharge. CTIs can include coordination between the different service providers (integrated care) and motivate patients to seek follow-up treatment independently by taking a closer look at their disorder (patient emancipation through psychoeducation) [13]. Systematic reviews on CTIs show a potential benefit for patients regarding risk of readmissions and symptom severity [14–17].

However, the literature shows that due to the high variability of a) intervention components, b) outcome measures, c) target groups/conditions, and d) methodological quality of the studies, there is not enough evidence to make a final recommendation for the use of CTIs. In addition, most of the included studies were conducted in the USA, where funding, organisational and health care structures differ from those in many other countries, e.g. those in Central Europe [18]. It is also not yet evident whether CTIs are cost-effective. The few studies that included cost-effectiveness analyses came to inconclusive and/or non-significant results. This is partly because the individual interventions were designed very differently (e.g. internet-based programme, peer support, clinician support) [19–22]. Nevertheless, within these broad variations of interventions components seem to be consistently effective. Therefore, we combined these components and developed a CTI to support patients with depressive and/or anxiety disorders at the transition from inpatient to outpatient psychosocial care.

To prepare the ground for a future effectiveness trial, we will conduct a randomised trial assessing the feasibility of the study procedures and the acceptability of a CTI conducted by a Care Transition Navigator (CTN) within the German health care system.

## Methods and analysis

### Study setting

The main setting of this feasibility trial are German hospitals in Southwest Germany (Federal State of Baden-Wuerttemberg). Inpatients will be recruited from mental healthcare wards and day clinics in German hospitals, where, patients with a wide range of mental disorders, from depression and anxiety disorders to eating disorders and obsessive-compulsive disorders receive treatment with a focus on intensive psychotherapy.

### Study design

This study is an individually randomised feasibility trial. After the inclusion of patients, the individual intervention period will be three months; for the total recruitment time 6 months are planned. There will be two main measurements; a baseline assessment just prior to randomisation and a post assessment three months after inclusion. There will be two follow-up measurements at six and nine months after inclusion which focus on the medium-term effects. Patient recruitment August 2022 and will probably be completed in September 2023. Data collection will probably be completed by May 2024. The study protocol is reported and implemented according to Standard Protocol Items: Recommendations for Interventional Trials (SPIRIT) guidelines (S1 File) [23].

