After discharge, further CTI sessions will take place between the patient and the CTN, during which barriers on the patient’s side will be continuously identified and addressed. Additionally, if necessary the CTN will reflect on the ambivalence towards follow-up treatment with the patient, to build motivation. In the first month after discharge, there will be two CTI sessions; in the months two and three after discharge, there will be one CTI session per month. If a patient successfully takes up outpatient follow-up treatment before the fifth CTI session, at least one further CTI session will be offered for joint final reflection and assessment of the sustainability of follow-up treatment. If the patient needs more structuring of the intervention, a patient-centred written brief discharge plan will be jointly developed by the patient and the CTN. This will help to (1) clarify the need and (2) the desired design of a follow-up treatment, (3) identify possible barriers, (4) identify patient’s areas/problems in particular need of support by the CTN, and (5) schedule the session dates between patient and CTN (1^st^ month two sessions, 2^nd^ and 3^rd^ month one session each). To support and motivate the patient, the CTN can screen for psychosocial services and treatment possibilities in the vicinity of the patient’s home. Furthermore, the patient will be motivated to contact the general practitioner after discharge and to inform him/her about the further course of treatment. Further components for support and motivation can vary individually depending on the symptom severity and the resources of the patient, but will include components of the following spectrum: systematic reminders about doctor’s appointments and medication intake, screening for suicidal ideation, evaluation of already known and/or newly emerging barriers, psychoeducation regarding the handling of mental disorders and coping strategies and behavioural activation (maintaining a positive attitude, solution orientation, stimulation of self-help). These optional components have been shown to be effective in several comparable studies [14, 17]. The CTI sessions will be conducted via a secure (i.e., encrypted), web-based videoconferencing platform on a subscription basis (arztkonsultation ak GmbH) and will last between 30 and 60 minutes. Subscription fees are covered by the trial funding. No fee will apply for patients. In routine care in Germany, the use of teleconferencing systems is covered by the statutory health insurance. During the intervention period, the CTN will attend a case supervision session led by a senior physician every two weeks, where all patients will be discussed. In particular, it will be discussed how to deal with hard-to-reach and less adherent patients to successfully implement the transition to outpatient psychosocial follow-up treatment in this group as well.

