### Recruitment

Patients will be recruited during their inpatient / day clinic stay in mental healthcare departments of German Hospitals. Suitable patients will be approached by their case leading therapist on the ward / day clinic during the regular therapy sessions three weeks prior to discharge. Here they will be informed about the study and provided with the study documents, consisting of information leaflet and the consent form in duplicate. If the patient agrees to receive further information, they will have a meeting with the CTN two weeks prior to discharge. During this meeting the CTN will 1) describe the study procedures to the patient, 2) address any remaining questions the patient may have, 3) obtain written informed consent, 4) collect the patient’s baseline data (either by filling out the questionnaire or through an online assessment), 5) allocate the patient to one of the two study conditions via an online randomisation platform, 6) inform the patient of the outcome of the randomisation, and, 7) if randomised to the intervention condition, arrange a first appointment (CTI session), which must still take place during the inpatient stay. If inclusion in the study is not possible, this will be documented with the reason and the patient’s age and gender. The CTN informs the case leading therapist on the ward of the outcome result of the randomisation.

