### Randomisation

After obtaining informed consent, patients will be randomly allocated to one of the two study conditions (treatment-as-usual, TAU vs. care transition intervention) in a 1:1 ratio. To ensure a seamless inclusion process, the CTN will conduct the randomisation during the initial recruitment meeting with the patient and subsequently inform the patient of the outcome. Concealment of the treatment sequence up to allocation will be assured via a secure web-based randomisation system (Randomizer, https://randomizer.at) operated by a data manager, not involved in the patient recruitment, centrally at the Department of General Internal Medicine and Psychosomatics, Heidelberg University. The treatment sequence is generated through a computer-generated sequence of random numbers. Randomisation will be stratified by depression and anxiety symptom severity at baseline as measured with the PHQ-ADS (three levels: minimal/mild, moderate, severe).

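### Sessions are counted from discharge but the post assessment from inclusion, so the fifth CTI session can fall up to about 14 days after the post assessment

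*Protocol article*

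**What the plan says.** Protocol article, Study design: after inclusion, "the individual intervention period will be three months", and the two main measurements are "a baseline assessment just prior to randomisation and a post assessment three months after inclusion". The section on patients' health status repeats that the post and follow-up measurements are timed from inclusion, at months 3, 6 and 9.

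Recruitment: interested patients are told that "they will have a meeting with the CTN two weeks prior to discharge". Consent, baseline and allocation all take place there. Randomisation confirms that "the CTN will conduct the randomisation during the initial recruitment meeting with the patient".

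The first session is arranged at the same meeting: "arrange a first appointment (CTI session), which must still take place during the inpatient stay". The rest are timed in the Intervention section: "In the first month after discharge, there will be two CTI sessions", and "in the months two and three after discharge, there will be one CTI session per month". That section also allows for an early finish: "If a patient successfully takes up outpatient follow-up treatment before the fifth CTI session, at least one further CTI session will be offered".

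**The concern.** The plan runs on two clocks. The stated intervention period and all assessments start at inclusion. Four of the five sessions start at discharge, about two weeks later. Nothing in the article text makes the post assessment wait for the fifth session, or confines that session to the early part of month three.

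The label 'post' implies a measurement after the intervention. For some CTI patients it may be taken while one session is still to come. Time since discharge, which is the time available to start outpatient care, also depends on how long the patient stays on the ward after inclusion.

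This matters mainly for what is carried forward. The Intervention section names treatment engagement as the primary outcome of the later confirmatory trial, and the Measurements section says procedures are tried out as they would run there. A three-month uptake figure from this trial is an obvious planning input, and the same schedule could be copied into the main trial.

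**Working it through.** **Inputs from the article**
- Inclusion (consent, baseline, randomisation): day 0, 14 days before discharge (Recruitment, Randomisation).
- Session 1: before discharge, so between day 0 and day 14 (Recruitment).
- Sessions 2 and 3: month one after discharge; session 4: month two; session 5: month three (Intervention).
- Post assessment: three months after inclusion (Study design).
- 50 patients allocated 1:1, so about 25 in the CTI arm (Abstract).

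**The stated figure.** With month length m and lead L (days from inclusion to discharge), the latest end of the session schedule is L + 3m. Counted from discharge this is 3m, which reproduces the stated three months. Counted from inclusion, as Study design words it, it is (14 + 3 × 30.44)/30.44 = 105.3/30.44 = 3.46 months. With 28-day months it is (14 + 84)/28 = 3.50 months.

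**Session 5 against the post assessment**, m = 30.44, L = 14:
- Window for session 5: 14 + 2 × 30.44 = day 74.9, to 14 + 3 × 30.44 = day 105.3.
- Post assessment: 3 × 30.44 = day 91.3, which is 91.3 − 14 = 77.3 days, or about 2.5 months, after discharge.
- Largest gap: 105.3 − 91.3 = 14 days. Algebraically (L + 3m) − 3m = L, so the gap always equals the lead.
- Share of the window after the post assessment: L/m = 14/30.44 = 46%.

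| Month length (days) | Lead (days) | Post assessment (day) | Session 5 window (day) | Largest gap (days) | Share of window after post |
|---|---|---|---|---|---|
| 30.44 | 14 | 91.3 | 74.9 to 105.3 | 14 | 46% |
| 30 | 14 | 90 | 74 to 104 | 14 | 47% |
| 28 | 14 | 84 | 70 to 98 | 14 | 50% |
| 30.44 | 7 (assumed) | 91.3 | 67.9 to 98.3 | 7 | 23% |
| 30.44 | 21 (assumed) | 91.3 | 81.9 to 112.3 | 21 | 69% |

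The article gives only the 14-day lead; the last two rows show sensitivity.

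**From share to patients.** If session 5 were spread evenly over month three and all 25 CTI patients received it, 0.46 × 25 = 11.5 patients would have it after the post assessment. Both conditions are assumptions.

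**Later assessments.** Six months after inclusion is 6 × 30.44 = day 182.6, which is 182.6 − 105.3 = 77 days after the latest session 5. The nine-month assessment is later still.

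**The case against.** The strongest reply is that the two sections can both be honoured. The Intervention section asks for one session in month three; it does not say that sessions run to the end of that month. A fifth session between about day 75 and day 91 satisfies both it and the three-month period in Study design, and precedes the post assessment. This stands. A reader might infer a flat contradiction, but what the text shows is an unresolved overlap: early timing is permitted and not required.

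A reader might also infer that the trial's main outcome is measured on incompletely treated patients, or that late sessions go unrecorded. The article does not support either. Its outcomes are recruitment yield, consent, retention, adherence, acceptance and documentation, and most of these do not depend on the post date. Adherence is calculated from scheduled and conducted sessions, and the CTN documents every session, so neither relies on the telephone interview. Clinical and service-use data are descriptive only, without hypothesis tests, and are collected again at six and nine months.

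Counting both arms from inclusion is also a legitimate choice in itself: it is fixed at randomisation and identical across arms. And the flowchart, study schedule and intervention schematic are not shown, so further timing detail may exist there.

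What remains is that no text seen here keeps the fifth session ahead of the assessment labelled 'post'.

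**Conclusion.** The point holds as a mismatch of time origins. On the protocol's own two-week lead, session 5 can fall up to about 14 days after the post assessment, and this gap does not depend on the month length used. For some CTI patients the descriptive three-month service-use and symptom data may therefore precede the end of the intervention.

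The number affected cannot be fixed from the document. It is tempting to read the arithmetic as 11 or 12 of 25 patients, but that requires an even spread over month three and a fifth session for everyone. The article expects some patients to take up treatment before the fifth session, and they may finish sooner.

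The impact is moderate to minor for this trial. It would be larger if the three-month uptake figure, or the schedule itself, were carried unchanged into the confirmatory trial.

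**What to change.** Leave the session timetable as it is and change the assessment clock.

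1. Reconcile the three-month intervention period in Study design with the session timing in Intervention, naming one origin.
2. Record the planned discharge date before randomisation and schedule the assessments in both arms from it, with the post assessment three months after that date. The post assessment then coincides with the latest end of the session schedule (both at day 105.3 with a 14-day lead, gap 0). Using the planned date keeps the origin independent of allocation; a gap can still arise where actual discharge is later than planned. A later fixed date counted from inclusion is weaker: 15 weeks (15 × 7 = 105 days) covers only a two-week lead.
3. If assessments have already begun and the inclusion-based schedule is kept, so as not to mix two schedules, state that the post assessment may precede session 5, report how many CTI patients this affected, and use the six-month data for uptake after the completed intervention.

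The cost is a sentence or two and a revised interview calendar, with each assessment and the study end about two weeks later. The projected end of data collection needs updating in any case: recruitment ending in September 2023 plus nine months is June 2024, against the May 2024 given in Study design. Option 3 costs only a sentence and one count in the report.

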### Inclusion and exclusion criteria

CTIs have not been evaluated or even implemented in German routine mental healthcare. Indeed, in reviews on transitional interventions not a single trial from Germany was included [15, 16]. Hence, we selected depression and anxiety as highly prevalent mental health disorders with high burden of disease to pilot the CTI in German mental healthcare. Inclusion criteria require inpatients to 1) have a recommendation by the case leading therapist on the ward to start an outpatient psychosocial follow-up treatment, 2) be treated for at least a moderate depressive and/or anxiety disorder (additional comorbid mental health disorders allowed), 3) agree to participate in the study by written informed consent, 4) be capable of giving consent and 5) be 18 years or older. Exclusion criteria are as follows: 1) planned resumption of outpatient psychotherapy after the inpatient stay which has been initiated before admission, 2) acute psychotic symptoms, e.g., persecutory delusions and/or thought insertion, 3) severe cognitive impairment or dementia, 4) significant hearing and/or visual impairment, 5) pregnancy in the ≥ 2nd trimester, and 6) insufficient German language proficiency. For this pilot trial, we aimed for minimizing the rate of loss-to-follow-up. Thus, we excluded pregnant women who may not have been able to complete follow-up assessments due to giving childbirth. We will drop this exclusion criterion in the main trial. Before enrolling patients, we will regularly check with providers having delivered inpatient treatment if a therapeutic dialogue was possible and whether language proficiency had turned out as a problem during inpatient treatment. To ensure the correct assessment of inclusion criteria, we will work closely with the case leading therapist on the respective ward / day clinic to record the recommendation for follow-up treatment and the diagnosis for which the patient was admitted. All other inclusion and exclusion criteria will be assessed by a study team member as part of the initial screening process.

### Study procedures

Prior to patient recruitment, we will meet with the hospital staff and introduce the study. We will precisely outline, how each member of the ward team will be involved and how they will guide the patients through the study during the inpatient stay. Additionally, during the preparatory visit we will address remaining questions and provide the team with a study handbook that includes a comprehensive description of patient inclusion criteria. The case leading therapists on the respective ward / day clinic will then start recruiting patients by introducing the study to them during regular therapy sessions. We anticipate that the therapeutic alliance with the case leading therapist will promote patients’ willingness to participate in the study. If a patient is interested in participating, they will provide written informed consent and fill out the baseline questionnaire. Then patient’s names will be pseudonymized and patients will be randomly allocated to the intervention or the control condition. The study flow is depicted in Fig 1 and the study schedule is shown in Fig 2.

**Fig 1 pone.0291067.g001:**
[figure not shown]
Study flowchart.

**Fig 2 pone.0291067.g002:**
[figure not shown]
Study schedule. ^1^ Patient Health Questionnaire Anxiety and Depression Scale (PHQ-ADS) [24], ^2^ 12-Item Short-Form Health Survey (SF-12) [25], ^3^ Recovery Assessment Scale (RAS-G) [26], ^4^ Somatic Symptom Disorder–B Criteria Scale (SSD-12) [27].

Before the intervention starts, the CTN will attend a two hour-training session, during which they will be familiarised with strategies and practicalities pertaining to organising follow-up treatments for patients with depression and anxiety. We will also train the CTN in motivational interviewing and psychoeducation. Using motivational interviewing, we aim to encourage and empower the patients to take up follow-up treatment.

### Study conceptual framework

The AMBITION intervention targets the transition between an inpatient / day clinic stay and an outpatient follow-up treatment (Fig 3) and accounts for the five domains for factors influencing treatment adherence established by the World Health Organization (WHO): social and economic, healthcare system, therapy-related, patient-related, and condition-related [28]. The intervention unfolds across these factors by tightening coordination between inpatient and community mental healthcare.

